### Statistical analysis

Given the ongoing advances in statistics and technology, all analyses will be performed in line with best current practice. Following the CONSORT statement [78], all our analyses will adhere to the intention-to-treat (ITT) principle (i.e., with an analysis of all patients as randomized). To this end, analyses of treatment effects will be conducted with multilevel mixed modelling, with treatment condition as factor and the depended measure as baseline covariate, while missing observations will be multiply imputed (with chained equations) for the health-economic analyses. In addition, we will also report the results in the per-protocol sample (≥ 6 supervised exercise sessions). Generalized (logit) mixed modelling will be used to compare the conditions on number of patients in remission at each follow-up measure. To examine whether rumination, self-esteem and memory bias are the mechanisms of change between adjunct exercise treatment and a decrease in depressive symptoms, multilevel structural equations modelling will be performed in Stata [79], or alternatively Hayes’ PROCESS macro [80] for SPSS [81] will be used.

Finally, a cost-effectiveness analysis (CEA) and cost-utility analysis (CUA) will be performed from a societal perspective [78]. We will consider four types of costs: 1) intervention costs, 2) healthcare costs, 3) patients’ and family out of pocket costs and opportunity costs of informal care, 4) productivity losses stemming from absenteeism and lesser efficiency while at work (presenteeism). The incremental cost-effectiveness ratio (ICER) will be computed to obtain the incremental costs per treatment responder and per QALY gained. Stochastic uncertainty will be handled using 2500 non-parametric bootstraps and by plotting the simulated ICERs on the ICER plane. For decision-making purposes, the ICER acceptability curve will be plotted for various willingness-to-pay (WTP) ceilings for making judgements whether the adjunctive exercise intervention offers good value for money relative to the care as usual comparator condition. One-way sensitivity analyses directed at uncertainty in the main cost drivers and outcomes will be performed to assess the robustness of our findings. Both the analysis and reporting of the findings will conform to the CONSORT [82], the Dutch guidelines for economic evaluations in health care, and CHEERS statements [78, 83]. All health-economic analysis will be conducted in R or Stata/SE 16.1 or later [79].

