**Methods:**

The present study is designed as a multicenter randomized superiority trial in two parallel groups with follow-up assessments up to 15 months. Currently depressed outpatients (*N* = 120) are randomized to guideline concordant Standard Care (gcSC) alone or gcSC with adjunct exercise treatment for 12 weeks. Randomization is stratified by gender and setting, using a four, six, and eight block design. Exercise treatment is offered in accordance with the NICE guidelines and empirical evidence, consisting of one supervised and two at-home exercise sessions per week at moderate intensity. We expect that gcSC with adjunct exercise treatment is more (cost-)effective in decreasing depressive symptoms compared to gcSC alone. Moreover, we will investigate the effect of adjunct exercise treatment on other health-related outcomes (i.e. functioning, fitness, physical activity, health-related quality of life, and motivation and energy). In addition, the mechanisms of change will be studied by exploring any change in rumination, self-esteem, and memory bias as possible mediators between exercise treatment and depression outcomes.

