### Sample size calculation

A recent meta-analysis on the effectiveness of exercise interventions compared to non-exercise comparators in adult outpatients with MDD [10] reports an overall medium to large effect on depressive symptoms, with Hedges’s g = 0.79. This meta-analysis included 11 trials, investigating both exercise as adjunct treatment to gcSC and exercise as monotherapy for depression. In order to provide the most optimal effect size estimate, we conducted our own meta-analysis, including only the trials examining the augmenting effect of exercise, to synthesize the available evidence from the most comparable trials. We identified four studies (moderate/high level of evidence; GRADE) [53] with similar designs to the present RCT that evaluated aerobic exercise as adjunct to gcSC in unipolar depressed mental health care outpatients, with depressive symptom levels as outcome [54–57]. The meta-analysis yielded a Hedge’s g effect size of 0.98 (95%CI = 0.51 ~ 1.45), se = 0.26, *t* = 3.84, *p* = .032, with only moderate heterogeneity, I^2^ = 37%. One study by Rueter and colleagues [56] appeared an outlier (based on the Galbraith plot). When removing this study to account for variations across studies, heterogeneity disappeared with I^2^ = 0%, while the effect size was similar to the original meta-analysis, including 11 trials (g = 0.79; 95%CI 0.42 ~ 1.17; se = 0.190; *p* = .053). Based on the latter, we assumed a between-group effect size of g = 0.70 for the power analysis.

The power calculation was based on guidelines offered by Hemming et al. [58] and accounted for the hierarchical data structure with patients being clustered in psychomotor therapists with a mean cluster size of *N* = 10 (range 5 ~ 15) [59] and an intra-cluster correlation of 0.05 [60], which introduces a design effect of 1.48. In addition, we assumed a correlation between baseline depressive symptoms and the relevant follow-up of *r* = 0.30 for the planned baseline-adjusted multilevel mixed analysis. In order to be able to detect an effect size g ≥ 0.70 as statistically significant at α < 0.05 (two-sided) with a power of (1-β) = 0.80, power analyses revealed a required minimum *N* = 60 per arm (*N* = 120 in total).

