**Fig. 1 Fig1:**
[figure not shown]
CONSORT flow chart

Patients in the gcSC with adjunct exercise condition start the exercise treatment simultaneously to the gcSC treatment (with a maximum two-week difference between start dates). Patients complete the baseline assessment in the week before the first treatment session. The surveys are sent via email using the online cloud-based data solution program, Castor EDC and can be filled out via any personal device (e.g. computer, tablet). This program is also used for the Case Report Forms and initial data management. Additionally, patients receiving the adjunct exercise treatment fill out a short questionnaire before and after each supervised exercise session on paper, as part of the treatment. An overview of the assessments can be found in Table 1 and Fig. 1. Expected study duration is 36 months. Inclusion of patients started in March 2020.

**Table 1 Tab1:** Assessment schedule

		Time point								
Endpoints	Material	T0	T1	T2	T3	T4	T5	T6	T7	T8
Primary outcome	IDS-SR	X	X	X	X	X	X	X	X	X
Secondary outcomes	SCID-5-S					X	X	X	X	X
	IPAQ	X	X	X	X	X	X	X	X	X
	Fitness^a^	X				X				
	WHODAS	X				X				X
	MEI-SF	X				X				X
Economic evaluation	EQ-5D-5L	X				X	X	X	X	X
	Tic-P	X				X	X	X	X	X
Mechanisms	RRS	X	X	X	X	X	X	X	X	X
	RSES	X	X	X	X	X	X	X	X	X
	SRET	X				X				X

^a^Assessed in 15% of randomly selected patients from both conditions

*IDS-SR* Inventory of Depressive Symptomatology (i.e. depressive symptoms)*, SCID-5-S* Structured Clinical Interview for DSM-5 (i.e. depressive remission), *IPAQ* International Physical Activity Questionnaire (i.e. physical activity), *WHODAS* World Health Organization Disability Assessment Schedule (i.e. disability), *MEI-SF* Motivation and Energy Inventory-Short Form (i.e. motivation and energy), *EQ-5D-5L* (i.e. quality of health), *Tic-P* Trimbos Institute and iMTA Cost questionnaire for Psychiatry (i.e. economic costs), *RRS* Ruminative Response Scale (i.e. rumination), *RSES* Rosenberg Self-Esteem Scale (i.e. self-esteem), *SRET* Self-Referent Encoding Task (i.e. memory bias)

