### Randomization

Randomization is stratified for gender and setting, using Castor EDC. This program consecutively enrolls patients in line with a four, six and eight block design. These blocks are created for both strata separately. The first block is generated with the first randomization and thereafter a new block is randomly selected and generated when the previous one is used up. Allocation of patients is randomly selected from the block in use. More information on the randomization algorithm can be found on the website of Castor EDC.^1^

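### The stated treatment-effect model omits gender and setting, on which randomisation is stratified; if they are prognostic, standard errors are slightly too large and the test is mildly conservative

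*Protocol article*

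**What the plan says.** Under Randomization the article states: "Randomization is stratified for gender and setting, using Castor EDC". The abstract says the same and adds that allocation proceeds "using a four, six, and eight block design".

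Under Statistical analysis, treatment effects are to be estimated by multilevel mixed modelling, "with treatment condition as factor and the depended measure as baseline covariate". Gender and setting appear nowhere in that section. The levels of the model are not listed. The only clustering unit named anywhere is the psychomotor therapist, under Sample size calculation.

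Two other analyses have their own descriptions. For remission: "Generalized (logit) mixed modelling will be used to compare the conditions on number of patients in remission at each follow-up measure". For the economic evaluation: "Stochastic uncertainty will be handled using 2500 non-parametric bootstraps". Neither description mentions covariates. Table 1 shows IDS-SR, EQ-5D-5L and Tic-P collected at T0, while SCID-5-S starts at T4.

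**The concern.** Stratified allocation forces the arms to be alike on gender and setting. If these factors predict depressive symptoms, the treatment contrast varies less than it would under simple randomisation. A model without them does not see that reduction: their contribution stays in the residual variance, and the reported standard error exceeds the true one.

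The article has not left the adjustment set of this model to a later document. It states the set, and the set does not match the design. What is at stake is precision and nominal test size: wider intervals than necessary and some lost power. Deciding on the strata before data are seen also removes a later choice between adjusted and unadjusted results.

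**Working it through.** **Inputs from the article (Sample size calculation).** 60 per arm; "α < 0.05 (two-sided"); power 0.80; design effect 1.48; baseline to follow-up correlation r = 0.30; and "we assumed a between-group effect size of g = 0.70 for the power analysis".

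**Assumed input.** R, the share of follow-up IDS-SR variance explained by gender and setting beyond the baseline score. The article gives no value, so 0 to 20% is shown.

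**The plan's own figures.**
- The design effect reproduces with ICC 0.05, mean cluster size 10 and a cluster-size coefficient of variation of 0.25: 1 + ((1 + 0.25²) × 10 − 1) × 0.05 = 1.481.
- The 60 per arm does not reproduce: 2 × ((1.960 + 0.842)/0.70)² = 32.04; × 1.48 = 47.41; × (1 − 0.30²) = 43.15, so 44 per arm. That is a separate matter. The present point does not depend on it, and 60 per arm is used below as the planned number.

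**Formulas, outcome SD = 1.**
- SE reported without strata: sqrt(2 × 1.48 × (1 − 0.30²)/60) = sqrt(2 × 1.48 × 0.91/60) = 0.2119.
- True SE when strata are balanced: sqrt(2 × 1.48 × (0.91 − R)/60).
- True alpha without strata: 2 × Φ(−1.96 × reported SE / true SE).
- Power without strata: Φ((0.70 − 1.96 × 0.2119)/true SE).
- Power with strata: Φ(0.70/true SE − 1.96).

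| R | True SE | Reported / true | True alpha, no strata | Power, no strata | Power, strata |
|---|---|---|---|---|---|
| 0% | 0.2119 | 1.000 | 0.050 | 0.910 | 0.910 |
| 5% | 0.2060 | 1.029 | 0.044 | 0.917 | 0.925 |
| 10% | 0.1999 | 1.060 | 0.038 | 0.923 | 0.938 |
| 20% | 0.1872 | 1.132 | 0.027 | 0.936 | 0.962 |

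Example at R = 10%: 0.2119/0.1999 = 1.060; 2 × Φ(−1.96 × 1.060) = 0.038. The power gains are 0.8, 1.5 and 2.6 points at 5, 10 and 20%.

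**Simulation check.** N = 120; six settings by gender (six is an assumption); permuted blocks of 4, 6 and 8; patient-level analysis of covariance without therapist clustering; 3000 runs per scenario. The Monte Carlo error near 0.05 is sqrt(0.05 × 0.95/3000) = 0.004.

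| R | Type I error, no strata | Type I error, strata |
|---|---|---|
| 0% | 0.047 | 0.047 |
| 5% | 0.037 | 0.043 |
| 10% | 0.034 | 0.048 |
| 20% | 0.028 | 0.051 |

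At R = 10% without strata, the mean reported SE was 0.1745 against an empirical SD of 0.1657. With strata the two agreed (0.1650 and 0.1651). The direction and rough size match the formulas even though blocks in small strata are often incomplete.

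**Economic side, illustration only.** Assume a utility SD of 0.25. A one-SE chance difference at T0 is 0.25 × sqrt(2/60) = 0.046. T0 utility carries half of the first three-month interval, 0.125 years, so the QALY difference moves by 0.046 × 0.125 = 0.006. If half of the difference persisted over the remaining 1.125 years, the shift would be 0.046 × (0.125 + 0.5 × 1.125) = 0.03.

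**The case against.** The strongest reply is that the effect is small, errs on the safe side and rests on a variance share that the article does not give. At 0% there is no effect, and at the design value g = 0.70 the gain stays within about 1.5 points unless the strata are strongly prognostic. That stands, and it limits the weight of the point.

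Second, the model is multilevel with unnamed levels. A random effect for site, or for therapists working within sites, could absorb part of the setting variance. That also stands in part, but no such effect would absorb gender, and the only cluster named is the therapist. The general commitment to best current practice does not replace the terms actually listed.

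Third, a reader might infer that the remission and economic analyses leave usable baseline values out, or that the baseline-covariate rule fails for remission because SCID-5-S has no T0 value. The document does not support this. The baseline rule belongs to the sentence on mixed modelling of treatment effects; remission has its own sentence and its own model, which does not repeat that rule. The economic text neither includes nor excludes adjustment. In a condensed article, such covariate lists are commonly left to the full protocol or analysis plan.

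The percentages above also do not carry over to a logit model, where adding prognostic covariates changes the conditional odds ratio and typically increases the standard error of its logarithm. A chance T0 imbalance in utility or costs is sampling variation that the bootstrap is meant to express. It concerns precision and is not a systematic error.

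**Conclusion.** The mismatch is real for the stated treatment-effect model: allocation is stratified by two factors and the listed terms contain neither. The consequence is a modest loss of precision and a conservative test. A reader might infer bias or false positives from an analysis that ignores its stratification; in the linear model neither follows, and the calculation points the other way.

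The size holds under three assumptions: the strata explain 5–10% of IDS-SR variance beyond baseline, blocks keep them close to balanced, and no random effect already takes up the setting variance. Remission and the economic evaluation offer room for improvement but contain no error on this point. It is worth correcting mainly because the correction is nearly free.

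**What to change.** State in the analysis plan that the mixed models for IDS-SR and the other continuous outcomes include gender and setting alongside condition and the baseline value, with setting as a fixed or random effect. Define setting. If it means the six recruiting locations listed under Procedure, fixed effects cost five degrees of freedom, plus one for gender, out of 120 patients; a random effect for setting costs less. All variables are already collected, so only wording changes.

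Two secondary suggestions, to be made only if the full plan does not already cover them:
- Name T0 IDS-SR as a covariate in the remission model, since SCID-5-S has no T0 value. Fixed effects for many settings could be sparse with a binary outcome, so the form of setting needs more care there.
- Within each bootstrap replicate, estimate incremental QALYs and costs by regression on arm, T0 EQ-5D-5L utility and T0 Tic-P costs, to gain precision.

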## Discussion

The aim of the present study is to examine the (cost-)effectiveness of adjunct exercise treatment in the outpatient treatment of depression. We will also investigate long-term effects up to 15 months and the effect of exercise on additional outcomes such as physical activity and fitness, disability, health-related quality of life and motivation and energy. Finally, we aim to examine potential mechanisms of change, focusing on the major cognitive and psychosocial processes contributing to depression i.e. rumination, self-esteem, and memory bias.

### Strengths and limitations

This study has several strengths. The RCT has the potential to provide a meaningful contribution to the literature on the cost-effectiveness and working mechanisms of an exercise prescription for the treatment of depression. The prospective study design enables us to follow patients for a period of 15 months post-baseline, to also examine the longer-term effects of exercise on depression. Finally, through the randomized design we will be able to compare whether adjunct exercise alongside usual care is more effective in decreasing depressive symptoms than gcSC alone. Because we provide the exercise intervention via psychomotor therapists and nurses who are already experienced in providing physical activity interventions, and do this within the naturalistic treatment setting, the RCT optimally facilitates later implementation of the evidence-based exercise protocol.

We further stimulate implementation in the (Dutch) mental health care system by flanking the RCT with a qualitative implementation study. The implementation study is two-folded. The first part will be used for scaling up and improving the implementation of an exercise augmentation prescription during the study. Psychomotor therapists/nurses, therapists who referred patients to the study, and patients who participated in the exercise treatment as well as patients who refused participation are interviewed to share their experiences. This allows for the identification of barriers and facilitating factors from an organisational level as well as an individual (patient) level. These results will be translated immediately to daily practice to enhance the implementation of prescribed exercise already during the RCT. The second part of the implementation study will identify facilitators and barriers for nationwide implementation once the current study shows (cost-)effective results. This will be based on (group-based) interviews with stakeholders who participated in the current research and for example with insurance companies and the clinical guidelines for depression treatment committee. The final results of the implementation study will be summarized in an implementation plan for future rollout.

Despite these strengths, there are some limitations that should be considered. First, patients in both conditions receive usual care in accordance with the Dutch multidisciplinary guidelines. While this reflects clinical practice, treatment heterogeneity in the gcSC is expected, as different psychological and/or pharmacological interventions are provided in different dosages and in varying formats (e.g. either group-based or individual CBT). Therefore, we can only draw general conclusions about the degree in which gcSC is augmented and merely explore which type of treatment is augmented most by exercise treatment. Nonetheless and due to the randomized design, the heterogeneity in gcSC should be similar across conditions, thus not thwart the study’s internal validity, while at the same time it increases the external validity of this pragmatic trial. Another benefit of a pragmatic trial is that future results can be optimally generalized and it facilitates the implementation of exercise in clinical practice, if proven (cost-)effective.

Other limitations are that exercise treatment is implemented as add-on treatment to gcSC which might lead to improvements in depressive symptoms due to nonspecific therapy effects such as more attention by therapists or peer support. The use of the Fitbit can also act as a co-intervention in the context of this trial, as it provides personal physiological feedback to patients in the exercise treatment condition. Finally, because patients decide whether they want to participate, there might be a selection bias due to the voluntary nature of the intervention. One may expect that patients who have a positive attitude toward exercise are more likely to participate. We register the reasons for refusal to participate and will explicitly invite patients who did not want to participate for our qualitative implementation study, in order to address the self-selection issue. Importantly, even if exercise treatment only attracts certain individuals, it can be an effective treatment module for depression, not limiting the additional value of this study in examining an accessible and acceptable treatment for depression.

### Clinical implications

Even though exercise as treatment for depression is proven effective and recommended in the NICE guidelines [61], it is generally not implemented following evidence-based guidelines, in Dutch (and international) clinical practice, neither is it included in educational programs of mental health care providers. This study will not only facilitate the implementation of prescribed exercise treatment but also aims to contribute to the much-needed improvement of MDD treatment outcome in an acceptable, effective, and cost-effective way.

## Data Availability

Not applicable.

## Abbreviations

MDD: Major depressive disorder
gcSC: guideline concordant Standard Care
WHO: World Health Organization
CBT: Cognitive behaviour therapy
IPT: Interpersonal therapy
RCT: Randomized controlled trial
APA: American Psychological Association
PAR-Q: Physical Activity Risk Questionnaire
PI: Principal investigator
CI: Coordinating investigators
IDS-SR: Inventory of Depressive Symptomatology-Self Report
SCID-5-S: Structured Clinical Interview for DSM-5
IPAQ: International Physical Activity Questionnaire
WHODAS: World Health Organization Disability Assessment Schedule
QALY: Quality-adjusted life-years
MEI-SF: Motivation and Energy Inventory-Short Form
Tic-P: Trimbos Institute and iMTA Cost questionnaire for Psychiatry
RRS: Ruminative Response Scale
RSES: Rosenberg self-esteem scale
SRET: Self-Referent Encoding Task
ITT: Intention-to-treat
CEA: Cost-effectiveness analysis
ICER: Incremental cost-effectiveness ratio
